### 7.5.1 Back up Randomisation Process

In the event of a randomisation system failure, the centre should contact the coordinating team in CTRC (Monday to Friday between 9:00 to 17:00 excluding bank holidays) to try to resolve the problem. If the problem cannot be resolved, the CTRC will perform central randomisation and randomise the participant using the back-up randomisation system. The back-up randomisation system is an exact replica of the live system but is based on a standalone PC at CTRC.

### 7.5.2 Contacts Database

The 'contacts database', also called CASTLE Contact Management System, is a secure system hosted by the University of Liverpool designed to be used immediately after randomisation. The system sits between the randomisation system and the online PBS intervention and will collect the required personal and contact details from participants if they have:

- Been allocated to receive the PBS intervention

and/or

- Been selected for actigraphy (and consented to actigraphy)

The required details will be entered in the contacts database by the research team at site. A personal login username and password, provided by the CTRC, will be required to access the contacts database; designated research staff will be issued with their personal login and password upon completion of training in the use of the system. When all fields in the contacts database have been completed and submitted by the research staff at site, an email will be automatically generated and securely sent to:

- the primary carer of the participant, which will include a link to the PBS intervention online and log in details (if the participant is randomised to the PBS arm).

and/or

- the sleep research team at Oxford Brookes University to inform them that a participant has been added so they can view the address and contact the parent/primary carer to arrange the shipment of the actigraphs (if the participant is selected for actigraphy and has consented to this).

The system is password protected and accounts will only be generated for specific members of the sleep research team at Oxford Brookes University and CTRC members that need access to participant's details.

### **7.5.3 Qualitative Sub-Study Identifiers**

As an exception, the screening number will be used to identify qualitative sub-study participants (instead of their randomisation number) by the qualitative team. This will allow the sub-study to have an identifier for both main trial accepters and decliners that is unique.

## **7.6 Who is Blinded to Allocations**

Data analysts will be blinded after assignment to interventions by assignment of randomisation numbers to participants.

## 8 PARTICIPANT TIME LINE, ASSESSMENTS AND PROCEDURES

### 8.1 Participant timeline

#### 8.1.1 Schedule of Trial Procedures by Visit

Trial procedures are listed below organised per visit and order of priority.

##### 0 Months (Baseline) – visit 1:

- Written Informed Consent (and assent where appropriate)
- Review of Medical History and EEG results
- Assessment of Eligibility Criteria and confirmation of full eligibility
- Measurement of weight and height
- Review of seizure occurrence & hospital admissions
- Children's Sleep Habits Questionnaire (CSHQ) – *primary carer*
- CANTAB test (iPad) – *child*
- Health Related Quality of Life in Children with Epilepsy (CHEQOL) – *primary carer & child (≥8 years)*
- Strengths and Difficulties Questionnaire (SDQ) – *primary carer*
- CHU9D Questionnaire – *child*
- EQ-5D-Y Questionnaire – *child ≥ 8 years*
- EQ-5D-5L Questionnaire – *primary carer*
- Parenting Self Agency Measure (PSAM) 5 item version Questionnaire – *primary carer*

##### 0 Months (Randomisation) – visit 1:

- Randomisation to Trial Interventions
- Completion of Contact Details Database
- Confirmation of selection for the actigraphy subset

*(At home: actigraphs are sent to the participant's address for those in the subset. Dyads will wear the actigraphs for 1 week)*

##### 3 Months – visit 2:

- Confirm continuing trial intervention
- CSHQ Questionnaire – *primary carer*
- CANTAB test (iPad) – *child*
- CHU9D Questionnaire – *child*
- EQ-5D-Y Questionnaire – *child ≥ 8 years*
- Resource Use Questionnaire – *primary carer*
- EQ-5D-5L Questionnaire – *primary carer*
- PSAM Questionnaire – *primary carer*
- Review of seizure occurrence & hospital admissions
- Assessment of Adverse Events
- Completion of Follow-up CRF
- Completion of AED treatment CRF

- Completion of concomitant medications related to an adverse reaction CRF

*(At home: actigraphs are sent to the participant's address for those in the subset. Dyads will wear the actigraphs for 1 week)*

### **6 Months – visit 3:**

- Confirm continuing trial intervention
- Review of seizure occurrence & hospital admissions
- Assessment of Adverse Events
- Completion of Follow-up CRF
- Completion of AED treatment CRF
- Completion of concomitant medications related to an adverse reaction CRF

### **12 Months – visit 4:**

- Confirm continuing trial intervention
- CSHQ Questionnaire – *primary carer*
- CANTAB test (iPad) – *child*
- CHEQOL Questionnaire - *primary carer & child (≥8 years)*
- SDQ Questionnaire – *primary carer*
- CHU9D Questionnaire – *child*
- EQ-5D-Y Questionnaire – *child ≥ 8 years*
- Resource Use Questionnaire – *primary carer*
- EQ-5D-5L Questionnaire – *primary carer*
- PSAM Questionnaire – *primary carer*
- Review of seizure occurrence & hospital admissions
- Assessment of Adverse Events
- Completion of Follow-up CRF
- Completion of AED treatment CRF
- Completion of concomitant medications related to an adverse reaction CRF

*(At home: actigraphs are sent to the participant's address for those in the subset. Dyads will wear the actigraphs for 1 week)*

### **24, 36, 48 Months – visits 5, 6, 7:**

- Confirm continuing trial intervention
- CSHQ Questionnaire – *primary carer*
- CANTAB test (iPad) – *child*
- 
- CHEQOL Questionnaire - *primary carer & child (≥8 years)*
- SDQ Questionnaire – *primary carer*
- CHU9D Questionnaire – *child*
- EQ-5D-Y Questionnaire – *child ≥ 8 years*
- Resource Use Questionnaire – *primary carer*
- EQ-5D-5L Questionnaire – *primary carer*
- PSAM Questionnaire – *primary carer*

- Review of seizure occurrence & hospital admissions
- Assessment of Adverse Events
- Completion of Follow-up CRF
- Completion of AED treatment CRF
- Completion of concomitant medications related to an adverse reaction CRF

Table 2: Schedule of Trial Procedures

| Procedures                                                                                         | T0                    |               | T0 +3 months
(+/-2 weeks) | T0 +6 months | T0 +12 months | T0 +24 months  | T0 +36 months  | T0 +48 months  | T0 +X months
Unscheduled visits |
|----------------------------------------------------------------------------------------------------|-----------------------|---------------|------------------------------|--------------|---------------|----------------------------|----------------------------|----------------------------|------------------------------------|
|                                                                                                    | Baseline  | Randomisation |                              |              |               |                            |                            |                            |                                    |
| Written Informed Consent (and assent where appropriate)                                            | X                     |               |                              |              |               |                            |                            |                            |                                    |
| Review of Medical History and EEG results                                                          | X                     |               |                              |              |               |                            |                            |                            |                                    |
| Weight and height                                                                                  | X                     |               |                              |              |               |                            |                            |                            |                                    |
| Assessment of Eligibility Criteria and confirmation of full eligibility                            | X                     |               |                              |              |               |                            |                            |                            |                                    |
| CSHQ Questionnaire – primary carer                                                                 | X                     |               | X                            |              | X             | X                          | X                          | X                          |                                    |
| CANTAB test (iPad)- child                                                                          | X                     |               | X                            |              | X             | X                          | X                          | X                          |                                    |
| CHEQOL Questionnaire–primary carer & child (≥8 years)                                              | X                     |               |                              |              | X             | X                          | X                          | X                          |                                    |
| SDQ Questionnaire – primary carer                                                                  | X                     |               |                              |              | X             | X                          | X                          | X                          |                                    |
| CHU9D Questionnaire – child                                                                        | X                     |               | X                            |              | X             | X                          | X                          | X                          |                                    |
| EQ-5D-Y Questionnaire – child ≥8 years                                                             | X                     |               | X                            |              | X             | X                          | X                          | X                          |                                    |
| EQ-5D-5L Questionnaire – primary carer                                                             | X                     |               | X                            |              | X             | X                          | X                          | X                          |                                    |
| PSAM Questionnaire – primary carer                                                                 | X                     |               | X                            |              | X             | X                          | X                          | X                          |                                    |
| Resource use Questionnaire – primary carer                                                         |                       |               | X                            |              | X             | X                          | X                          | X                          |                                    |
| Randomisation to Trial Interventions                                                               |                       | X             |                              |              |               |                            |                            |                            |                                    |
| Completion of Contact Details Database                                                             |                       | X             |                              |              |               |                            |                            |                            |                                    |
| Actigraphy                                                                                         |                       | (X)           | (X)                          |              | (X)           |                            |                            |                            |                                    |
| Confirm continuing trial intervention
(as per randomisation or alternative anti-epileptic drug) |                       |               | X                            | X            | X             | X                          | X                          | X                          | X                                  |
| Review of seizure occurrence & hospital admissions                                                 | X                     |               | X                            | X            | X             | X                          | X                          | X                          | X                                  |
| Assessment of Adverse Events                                                                       |                       |               | X                            | X            | X             | X                          | X                          | X                          | X                                  |
| Completion of Follow-up CRF                                                                        |                       |               | X                            | X            | X             | X                          | X                          | X                          | X                                  |
| Review of AED treatments and concomitant medications related to adverse reactions                  |                       |               | X                            | X            | X             | X                          | X                          | X                          | X                                  |

 At baseline, written informed consent must be taken before performing any study procedures. Follow up will be a minimum of 12 months but can go beyond this, up to a maximum of 48 months, as trial timelines allow

(X) Measures only taken from the selected subset of patients that have consented to this activity

Table 3: Schedule of Sub-Study Interviews

**Trial accepters:**

| Procedures                                                                | Trial Randomisation (T0) | Interview 1 (T 2 - 4 weeks) | Interview 2 (T6.5-7 months) | Interview 3 (T12.5-13 months) |
|---------------------------------------------------------------------------|--------------------------|-----------------------------|-----------------------------|-------------------------------|
| Participants' contact details are sent to Edge Hill University (via CTRC) | X                        |                             |                             |                               |
| Sub-study written informed consent (and assent where appropriate)         |                          | X                           |                             |                               |
| Qualitative interviews (for those who consent)                            |                          | X                           | X                           | X                             |

**Trial decliners:**

| Procedures                                                                | Decision to not participate in the trial (T0) | Interview 1 (T 2 - 4 weeks ) | Interview 2 (T6.5-7 months) | Interview 3 (T12.5-13 months) |
|---------------------------------------------------------------------------|-----------------------------------------------|------------------------------|-----------------------------|-------------------------------|
| Participants' contact details are sent to Edge Hill University (via CTRC) | X                                             |                              |                             |                               |
| Sub-study written informed consent (and assent where appropriate)         |                                               | X                            |                             |                               |
| Qualitative interview (for those who consent)                             |                                               | X                            | X                           | X                             |

**8.1.2 Schedule for Follow-up**

The expected duration of follow-up for each participant is between a minimum of 12 months and a maximum of 48 months, depending on the time of recruitment. All participants will be followed up whether they are still taking their allocated treatment or not. Where participants default from hospital follow-up, additional information will be sought at the end of the trial from GPs who will be the main prescribers of AEDs in this trial, and where necessary participants will be contacted directly for follow up information.

Participants will be followed up as per routine clinical practice and typically at 3, 6, and 12 months and annually thereafter, where applicable. Participants will be seen at other times as clinically indicated.

A visit window for the 3 month visit of +/- 2 weeks is allowed. Visit windows are not prescribed for the 6, 12 months or annual visits after that. A delegated member of the research team should complete the 'follow-up CRF' for the 3, 6, 12 month and annual visits. The visit which occurs at the nearest timepoint will be taken to be the record of the 3, 6, 12 months or other annual visits from randomisation.

In the event of an early trial termination, the schedule for follow up activities (including actigraphy and qualitative interviews) will be shortened accordingly to 6 months post-randomisation. This will occur following agreement by the TMG, IDSMC and Sponsor.

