| To compare time to 12-month remission from seizures                                                      | Time to 12-month seizure remission based on seizure report                                                                                                                          | 3,6,12 months and annually thereafter 'when was last seizure' question in clinic |
| To determine if a PBS intervention is superior to standard care                                          | Total sleep problem score as measured by the CSHQ                                                                                                                                   | At 12 months and annually thereafter                                             |
| To compare measures of cognition across the different treatment groups                                   | Total score in three chosen assessments delivered by CANTAB iPad Neuropsychological battery                                                                                         | At baseline, 3 and 12 months and annually thereafter                             |
| To compare Health Related Quality of Life across the different treatment groups                          | CHEQOL score change (1)                                                                                                                                                             | At baseline and 12 months and annually thereafter                                |
| To compare measures of children's behaviour across the different treatment groups                        | Total score on strengths and difficulties questionnaire (SDQ)                                                                                                                       | At baseline and 12 months and annually thereafter                                |
| To identify any adverse reactions and their rate                                                         | Records of adverse reactions                                                                                                                                                        | Adverse reactions at 3,6,12,24 months and annually thereafter in clinic          |

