### 11.3 Sample Size calculation

#### 11.3.1 Drug Intervention

The primary outcome is time to 6-month seizure remission. A 5% two-sided significance level is used for each of two primary comparisons of interest: carbamazepine versus active monitoring and levetiracetam versus active monitoring. We have obtained individual patient data from the trial sponsor of the German HEAD study (30) to provide an estimated probability of being without remission on placebo at 6 months of 0.57. With 97 per group we would have 80% power to detect a reduction from 0.57 to 0.37 (Hazard Ratio=0.57). Inflating sample size to allow for 12% attrition requires total n=330.

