### 11.5.1 Primary and Secondary Outcomes

The primary outcomes are time to 6-month remission from seizures (for the hypothesis that carbamazepine or levetiracetam are superior to no AED) and change in CSHQ at 3 months (for the hypothesis that sleep behaviour intervention will be superior to standard care).

Following the principles discussed by Montgomery *et al.* (32), two separate regression analyses, one for each primary outcome, will be undertaken.

The interval (in days) from randomisation to occurrence of a 6-month remission will be summarised by Kaplan-Meier curves for each treatment group. A Cox proportional hazards model will be fitted with factors included for AED (CBZ, LEV vs no AED); sleep (intervention vs no intervention); baseline variables. The adjusted Hazard Ratio main effects of CBZ or LEV compared to no AED will be estimated and presented with a p-value and 95% confidence interval.

For the second primary outcome CSHQ, a linear regression model will be fitted with factors included for AED (CBZ, LEV vs no AED); sleep (intervention vs no intervention); baseline variables, including baseline CSHQ. The adjusted mean difference main effect of sleep intervention compared to no sleep intervention will be estimated and presented with a 95% confidence interval.

The impact of centre effect on the treatment comparison will be investigated by considering both fixed and random effects models. When analysing the data using the fixed effect approach, the centre effect is to be modelled by a series of dummy variables. However, due to concern regarding the number of dummy variables required, a random effects analysis will also be considered.

The primary analysis will address the principal research question focusing on treatment main effects. In secondary analyses the interaction between AED and sleep intervention will be investigated, recognizing that the precision of the estimates of interaction is very likely to be too poor for large effects to be ruled out.

All analyses will be reported in accordance with the CONSORT checklist (33) and regardless of statistical significance. There will be no correction for multiple comparisons (34).

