A similar strategy will be used for the analysis of secondary time to event outcomes. For time to treatment failure, further analysis will be undertaken to assess the two main reasons for treatment failure - inadequate seizure control and unacceptable adverse effects. To allow for possible dependence between the different withdrawal risks, cumulative incidence analyses will be presented (34).

The Haybittle-Peto approach will be employed for each interim analysis, with 99.9% confidence intervals calculated for interim analysis effect estimates. The final analysis will be undertaken at the end of the trial when all participants have a minimum 12 months follow-up data and 95% confidence intervals will be calculated.

QOL data will be analysed longitudinally to explore between treatments changes in scale scores over time, taking account of baseline QOL.

Qualitative interview data will be analysed using an interpretive, reflexive and conceptual analytical approach. Data will be thematically analysed in discrete sets (e.g., the trial group and the non-trial groups, different treatments/management, different responses/experiences), and parents/primary carers' and children's transcripts will be analysed separately before considering each dyad and prior to synthesis of all the data.

For the analysis of safety events, all participants who received any amount of each trial drug will be included in the safety analysis dataset in the treatment group they actually received. All safety events reported by the clinical investigators will be presented, identified by treatment group. Safety events will be grouped according to a pre-specified coding system and tabulated. The number (and percentage) of participants experiencing each safety event, and the number (and percentage) of occurrences of each safety event will be presented. No formal statistical testing will be undertaken.

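### On early termination, follow-up ends at the earliest time a 6-month remission can occur, so the primary time-to-event analysis becomes a yes/no comparison and a child last seen slightly early cannot be classified

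*Protocol*

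**What the plan says.** **The early-termination rule.** Protocol section 8.1.2 states that on early termination "the schedule for follow up activities (including actigraphy and qualitative interviews) will be shortened accordingly to 6 months post-randomisation". This follows agreement by the TMG, the IDSMC and the sponsor. The same section says of visit timing: "Visit windows are not prescribed for the 6, 12 months or annual visits after that". The visit nearest each timepoint is taken as its record.

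**The primary drug outcome.** Section 11.5.1 states: "The interval (in days) from randomisation to occurrence of a 6-month remission will be summarised by Kaplan-Meier curves for each treatment group". A Cox model then gives adjusted hazard ratios for each drug against no AED. The final analysis is placed at the point "when all participants have a minimum 12 months follow-up data".

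**The sample size.** Section 11.3.1 uses an "estimated probability of being without remission on placebo at 6 months of 0.57" and says: "With 97 per group we would have 80% power to detect a reduction from 0.57 to 0.37 (Hazard Ratio=0.57").

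**Other outcomes touched by the cut.** In Table 1 (section 3.3), CHEQOL and SDQ are both scheduled "At baseline and 12 months and annually thereafter". Table 3 places the second qualitative interview at 6.5 to 7 months. Section 8.4.1 places it 6 months after the first interview, which is itself at 2 to 4 weeks.

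**Early closure is foreseen.** Section 8.7 allows premature closure, and section 11.4 does not expect the trial to progress if pilot recruitment is under 50% of plan.

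**The concern.** A remission counted from randomisation cannot be complete before 6 months. If follow-up ends there, the study closes for each child at the moment the event first becomes possible. Three things follow.

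- A child with any seizure after randomisation cannot reach the event before the cut. This includes a seizure in the up to 14 days before treatment must start (section 7.5). Under the planned 12-month minimum, the same child could still go on to a 6-month remission.
- With no window on the 6-month visit, a seizure-free child whose last visit falls a few days early is censored before any event is possible.
- Outcomes first repeated at month 12 would have a baseline value only.

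An SAP can choose a tie rule or a binary summary. It cannot recover seizure dates or questionnaires that the schedule stopped collecting.

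**Working it through.** **1. Reproduce the plan's sample size.** Inputs from section 11.3.1: probabilities without remission 0.57 and 0.37, two-sided 5%, 80% power. With the mean probability 0.47:

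n = [1.960 × √(2 × 0.47 × 0.53) + 0.842 × √(0.57 × 0.43 + 0.37 × 0.63)]² / 0.20²

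= [1.960 × 0.706 + 0.842 × 0.692]² / 0.04 = 3.863 / 0.04 = 96.6, so **97 per group**, with power 80.2% at 97. Inflating for attrition: 3 × 97 / 0.88 = 330.7, against the stated 330. The plan's figures reproduce as a comparison of proportions at 6 months.

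**2. Earliest possible event.** The time origin is randomisation and the event is a 6-month remission, so the smallest event time is 6 months, about day 183. The early-termination cut is also 6 months. This takes seizure-free time as counted from randomisation; section 11.5.1 does not say that earlier seizure-free time counts.

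**3. The planned model when everyone is cut at 6 months.** Apply the plan's rates to 97 per arm: 0.43 × 97 ≈ 42 remissions on control and 0.63 × 97 ≈ 61 on drug, all at one tied time. Here a ratio above 1 means more remission on drug.

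| Analysis of the same data | Estimate | p |
|---|---|---|
| Cox, Breslow ties | HR 1.45 (= 61/42) | 0.063 |
| Cox, Efron ties | HR 1.70 | 0.008 |
| Logistic regression | OR 2.22 (= (61/36)/(42/55)) | 0.007 |

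The Cox model can be fitted, but it carries no timing information, and its significance turns on a computational choice. The comparison of proportions is well defined and keeps 80.2% power at 97 per arm.

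**4. Children last seen before 6 months.** Section 8.2.1 records the dates of the first and the most recent seizure since the previous visit. A child seen early who has already had a seizure is therefore a known non-remitter at 6 months. Only a seizure-free child seen early is undetermined. A child seen late can still be classified at 6 months from the recorded dates, so late visits do no harm and early ones do.

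The Protocol gives no distribution of visit dates, so the share seen early, f, is an assumption. Suppose early timing is unrelated to arm or outcome, and take 97 per arm for illustration. The undetermined children number f × 0.43 × 97 and f × 0.63 × 97. If they were counted as not remitted, the 0.20 difference would shrink to 0.20 × (1 − f).

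| f (assumed) | Undetermined, control | Undetermined, drug | Difference if counted as not remitted |
|---|---|---|---|
| 10% | 4 | 6 | 0.18 |
| 25% | 10 | 15 | 0.15 |
| 50% | 21 | 31 | 0.10 |

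Where the drug works, the undetermined children fall more heavily in the drug arm.

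**5. Other outcomes set against a 6-month cut.**

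| Outcome | Schedule | After a 6-month cut |
|---|---|---|
| CSHQ (second primary) | Baseline, 3 months | Intact |
| Time to first seizure | From 3 months on | Intact to 6 months |
| Time to 12-month remission | Needs 12 months | Not observable |
| CHEQOL, SDQ | Baseline, 12 months, annually | No follow-up value |
| Interview 2 | 6.5 to 7 months (Table 3) | After the cut, although the cut names interviews |

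**The case against.** The case on the other side is substantial, and most of it stands.

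- **The analysis is still possible.** A reader might infer that the drug comparison cannot be carried out. Step 3 shows otherwise: the Cox model fits, and the 6-month proportion that remains is the quantity behind the sample size.
- **Not everyone has a single event day.** Section 8.1.2 shortens the schedule. It does not say that data beyond 6 months are discarded, so children already past 6 months at termination can have later remission dates. A late visit can also record a later remission.
- **There is no contradiction with the 12-month minimum.** Section 11.5.1 describes the trial run as planned. Section 8.1.2 is an explicit exception that needs agreement from three bodies.
- **A loss of half the power does not follow.** It is tempting to assume that visits scatter evenly around day 183 and to discard half of each arm. The Protocol supports no such scatter, and step 4 shows that early-seen children with a seizure are already classified. Section 8.2.1 also takes seizure data at unscheduled visits, and section 8.1.2 allows GP or direct contact for defaulters.
- **Losing 12-month outcomes is a cost of stopping early.** Any cut before 12 months loses 12-month remission. Continuing to 12 months would undo the shortening that the rule exists to provide, so it is a trade-off and not a correction.
- **The choice of analysis often belongs in the SAP.** That is fair for the tie rule or effect measure. It does not cover the timing of the last contact or which questionnaires are given then, which the Protocol fixes.

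What survives is narrow. The cut coincides with the earliest event time, nothing keeps the last contact from falling before it, and two questionnaires lose all follow-up for want of being scheduled at that contact.

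**Conclusion.** The point holds as a cheap improvement to a contingency rule. It has no effect if the trial runs as planned.

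For participants cut at 6 months, the planned Kaplan-Meier and Cox analysis reduces to a yes/no comparison at 6 months. The Cox result then depends on tie handling (p = 0.063 or 0.008 on the same illustrative data). A seizure-free child last seen early is unclassifiable; how many there would be is unknown, because the Protocol gives no visit-date distribution. CHEQOL and SDQ have no follow-up value in these participants, and sections 8.1.2 and 8.4.1 and Table 3 do not fit together on the second interview.

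The binary comparison stays valid if last contacts are not early. It would have 80.2% power at 97 per arm. For assumed smaller numbers, power would be 52% at 50, 34% at 30 and 24% at 20 per arm, but that loss comes from reduced recruitment and not from the 6-month cut.

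The conclusion assumes that seizure-free time is counted from randomisation and that the cut is applied as written.

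**What to change.** Amend section 8.1.2 so that, on early termination:

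1. the last seizure-date contact is held no earlier than 6 full months after randomisation, for example between 6 months and 6 months plus 4 weeks;
2. CHEQOL and SDQ are completed at that contact;
3. all seizure data already collected beyond 6 months are kept;
4. the drug comparison for participants cut at 6 months is the proportion seizure-free for the 6 months since randomisation, supported by time to first seizure.

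Add to section 11.5.1 a sentence saying that the 12-month minimum and the Cox model apply to the trial run as planned, with a reference to this rule. Reconcile Table 3 and section 8.4.1 with section 8.1.2 by stating whether the second interview is brought forward, allowed after the cut or dropped.

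The cost is protocol wording, a last contact up to about 4 weeks later for some families, and two existing questionnaires moved to it.
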